#### Intervention Fidelity and Monitoring of Adverse Events

Before beginning this study, treatment therapists were trained by a member of the research team with a high-level experience in BMI training for stroke patients. During the whole duration of the study, the members of the research team and research coordinator randomly visited training sessions, to ensure that scheduled intervention was being performed accurately and with high adherence to the protocol proposed. Any adverse unpredictable event was recorded in the registry of each patient and the electronic database of the study and managed according to the policies of the hospital, with referral appropriate medical follow-up.

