##### Task-Specific Brain-Machine Interface Training

BMI training was conducted for approximately 40 min per session, 1 session per day, and 5 days per week, for 2 weeks.

The motor-driven orthosis was attached to the affected hand to achieve finger extension movement at the metacarpophalangeal and proximal interphalangeal joints. The orthosis was designed to remedy the finger position as the fingers arched with the thumb opposed, helping patients to hold or release objects. The thumb opposition position also helps maintain decreased flexor spasticity. The range of the angle in the orthosis action was adjusted by the examiner to avoid pain and spasticity. During the training, the motor-driven orthosis helped finger extension by a predetermined angle with 1659 Nmm at maximal torque. This setting allowed patients to perform task-specific training with BMI in a real-world setting.

A pair of disposable electrodes (25 × 45 mm) for electrical stimulation was placed over the belly of the paretic extensor digitorum communis muscle. Test stimulation (biphasic rectangular wave, pulse width of 1 ms, and frequency of 100 Hz) was then given, and the intensity was set at just above the motor threshold. Note here that this is a known intensity for recruiting Ia proprioceptive afferents of the stimulating muscle. Such NEMS of the target muscle of motor imagery contingent upon the occurrence of ERD may allow sensorimotor coactivation to be restricted to the target corticomuscular region and may foster plasticity and motor learning [39]. This should further help to selectively reinforce the sensorimotor representations.

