#### Statistical Analyses

The following 2 analysis populations are defined in this clinical trial. Statistical analyses were performed for each patient population.

The Full Analysis Set (FAS) essentially included all randomized patients, in accordance with the intention-to-treat principle, except for the following patients who violated major conditions in this study:

Patients who did not meet major inclusion criteria in this trialPatients who did not receive any study treatmentPatients who had no baseline measurements or no measurements after baselinePatients who withdrew informed consent after randomization and refused to generate any data in this trial

The Per Protocol Set (PPS) included patients who were compliant with the protocol and are defined in the patient-data handling document that will be finalized before the unblinding of this trial.

The primary analysis population in this trial is the FAS. The primary endpoint, a change from baseline in FMA at 28 days after study treatment, will also be analyzed for the PPS. The sensitivity of the primary analysis results will be examined via a comparison of results between the 2 analysis sets. All patients who received at least one study treatment are included in the safety analysis. The patient-data handling document, including the data handling rule for measurement at each time point, will be finalized before the unblinding. Methods to handle missing data will also be included in the statistical analysis plan (SAP) for this trial. Demographic factors and baseline characteristics are summarized by the treatment group.

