#### Safety Analysis

##### Adverse Events and Device-Related Problems

The safety primary endpoints in this study are proportions of adverse events and device-related problems. The number of events and the proportion will be calculated, and 95% CIs for the proportions will be estimated with the Clopper-Pearson method.

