#### Sample Size Estimation

The total sample size in this trial was set at 40 patients (20 per group).

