### Ethics and Dissemination

This study was conducted in accordance with Ministerial Ordinance on Good Clinical Practice for Medical Devices [59]. All participants provided voluntary written informed consent. Prospective participants were fully informed about what study participation involved and the potential benefits and risks. Ethics approvals had been obtained from the institutional review board of Keio University (protocol number: KCTR-D008, reference number: D16-03). In addition, for Saiseikai Kanagawa-ken Hospital, Tokyo Metropolitan Rehabilitation Hospital, and Tokyo Bay Rehabilitation Hospital, ethics approval had been obtained from the institutional review board of Saiseikai Kanagawa-ken Hospital (protocol number: KCTR-D008). Any protocol amendments will be submitted for ethical approval and communicated to the trial registry. The results of this study will be used to gain regulatory approval for the manufacture and sale of the medical device used in this study in Japan. After approval, the results will be presented at scientific meetings and published in journals.

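### The adverse-event recording sentence is limited to unpredictable events, but the primary safety endpoints carry no such limit; the two need to be reconciled

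*Protocol article*

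**What the plan says.** Capture is described once, at the end of the paragraph headed Intervention Fidelity and Monitoring of Adverse Events: "Any adverse unpredictable event was recorded in the registry of each patient", and in the study database. The word *unpredictable* is not defined. Device-related problems are not mentioned there.

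The endpoint is set under Adverse Events and Device-Related Problems: "The safety primary endpoints in this study are proportions of adverse events and device-related problems". The summary follows: "The number of events and the proportion will be calculated, and 95% CIs for the proportions will be estimated with the Clopper-Pearson method". Neither sentence mentions predictability.

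The safety population is given under Statistical Analyses: "All patients who received at least one study treatment are included in the safety analysis". Safety is a stated aim in the abstract and in Study Objectives, and Ethics and Dissemination says that the results will be used to seek regulatory approval of the device.

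The section on task-specific BMI training shows that at least some device effects were foreseen: "The range of the angle in the orthosis action was adjusted by the examiner to avoid pain and spasticity".

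**The concern.** The sentence that feeds the safety database is narrower than the endpoint computed from it. The qualifier, if it does anything, takes foreseeable events out of the described recording. For a device trial those are often the relevant ones: local discomfort under a motor-driven orthosis is easy to anticipate and still an adverse event when it happens. A site that left such an event out would not be departing from the sentence as printed.

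At stake are the primary safety proportions in a trial meant to support device approval. Any loss from a literal reading would probably not be even across arms, because control participants do not wear the orthosis.

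**Working it through.** **1. The two statements side by side.**

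| Element | Recording sentence | Safety endpoint |
|---|---|---|
| Adverse events, unpredictable | covered | counted |
| Adverse events, foreseeable | not covered, not expressly excluded | counted |
| Device-related problems | not mentioned | counted |

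The second and third rows are the mismatch. It lies between a stated rule and a stated endpoint; it does not depend on something the article omits.

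**2. Is there a foreseeable event to which this applies?** Yes. The orthosis angle is set with pain in mind, so pain from the orthosis was anticipated. Spasticity is named in the same place but is a weaker example: the Modified Ashworth Scale measures it at wrist and finger flexors at baseline, post-treatment and follow-up, whatever the adverse-event wording says.

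**3. Which arm would be affected?** Only the BMI arm wears the orthosis. The control section also says that no electrical stimulation was given during imagery. The abstract is less clear on stimulation, but the orthosis contrast does not depend on it. The direction is therefore plausible, though no data in the article confirm it.

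**4. Size.** The plan attaches no figure to the safety endpoint, so there is none to reproduce. The only usable input is the denominator: "The total sample size in this trial was set at 40 patients (20 per group"). It agrees with the sample-size rationale: 17 / (1 − 0.15) = 20.

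For x patients with an event out of n = 20, the Clopper-Pearson 95% limits are:

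- lower = 0.025 quantile of Beta(x, n − x + 1), or 0 if x = 0
- upper = 0.975 quantile of Beta(x + 1, n − x), which for x = 0 is 1 − 0.025^(1/20) = 0.168

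The event counts below are assumptions. Suppose that 6 of 20 patients in one arm had an event, and vary how many were foreseeable and unrecorded:

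| Unrecorded | Recorded x/20 | Estimate | 95% CI |
|---|---|---|---|
| 0 | 6 | 30% | 11.9% to 54.3% |
| 2 | 4 | 20% | 5.7% to 43.7% |
| 4 | 2 | 10% | 1.2% to 31.7% |
| 6 | 0 | 0% | 0% to 16.8% |

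With 20 per arm, each patient whose event is not recorded lowers the estimate by 1/20 = 5 percentage points. The interval reflects sampling error only and does not allow for incomplete recording. In the last row its upper limit, 16.8%, lies below the assumed 30%.

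**The case against.** A reader might infer that only unpredictable events were recorded, that expected device effects were missed, and that the safety proportions are biased downward. The article does not support that much.

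- The recording sentence affirms that certain events were recorded. It contains no *only* and excludes nothing. The endpoint sentence contains no *all*.
- The sentence is a one-line summary closing a paragraph on fidelity. Definitions, expectedness and reporting windows commonly sit in the full protocol, which is not shown. Their absence here is not a fault.
- The article says: "This study was conducted in accordance with Ministerial Ordinance on Good Clinical Practice for Medical Devices". Making adverse events and device problems primary safety endpoints also presupposes that both are collected.
- *Unpredictable* may be loose English for *untoward*. The article has other awkward phrasing.
- Adjusting the orthosis to prevent pain is a preventive setting, not a list of events exempt from recording.

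Most of this stands. It rules out any claim that events were lost, and it means the table above shows sensitivity to assumed counts and no more. It does not remove the mismatch. Condensing a longer document explains silence, but here the printed rule carries a restrictive adjective that the printed endpoint lacks. The content of the ordinance is not in the article, so it cannot settle what the sentence means. If the adjective is only loose wording, the text gives no way to tell, and deleting it costs nothing.

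**Conclusion.** The point holds as a wording inconsistency with a possible consequence for the data. The described recording is narrower than the primary safety endpoints, and device-related problems do not appear in it at all. If the sentence was followed literally, the safety proportions and their intervals could be too low, more likely in the BMI arm. That conclusion rests on two assumptions the article does not settle: that *unpredictable* was meant and applied as a restriction, and that foreseeable events occurred.

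No missed event is shown, and the size of any bias cannot be derived. The 5 percentage points per unrecorded patient is simply the arithmetic of 20 per arm.

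**What to change.** Reword the recording sentence in Intervention Fidelity and Monitoring of Adverse Events to say that every adverse event and every device-related problem, expected or not, is recorded in both arms. That brings it into line with the endpoint definition, which can stay as it is.

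Then establish what was actually done. If all events were recorded, nothing more is needed. If recording was restricted to unpredictable events, either check the source notes for expected events and device problems before the data are finalised, or state plainly that the reported safety proportions cover unpredictable events only. The Results section describes data correction as still under way, so at the time of writing the check was still possible.

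The cost is one sentence and, only if recording was restricted, a review of notes for at most 40 patients. The safety figures may come out slightly less favourable.

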#### Criteria for Withdrawal

Participants were withdrawn from the study in the event of any relevant deterioration in health likely to affect participation or if they withdrew their consent.

#### Outcome Measurement

#### Schedule of Assessment

The primary outcome measure was assessed by a blinded evaluator. Other functional measurements were assessed by evaluators who were trained by the organizer of this RCT. Most assessments were conducted at baseline, after intervention (post), and 4 weeks after intervention (follow-up). EEGs were recorded by the EEG-BMI rehabilitation system during each training session. The schedule of assessments is shown in Table 1.

**Table 1 table1:** Schedule of assessments.

Time points and measure		Baseline	Intervention (10 sessions during 2 weeks)	Posttreatment	Follow-up (4 weeks after treatment)
**Primary outcome measure**					
	Fugl-Meyer assessment	B^a^	—^b^	B	B
**Secondary outcome measure**					
	Action Research Arm Test	E^c^	—	E	E
	Motor Activity Log-14	E	—	E	E
	Stroke Impairment Assessment Set	E	—	E	E
	Modified Ashworth Scale	E	—	E	E
	Barthel Index	E	—	—	E
	Goal Attainment Scale	S^d^	—	—	S
	Stroke-Specific Quality of Life Scale	S	—	—	S
	Surface electromyography	EP^e^	—	EP	EP
	Electroencephalography during brain-machine interface or imagery training	—	EP	—	—

^a^B: assessment of blinded evaluator.

^b^Dashes indicate "not applicable."

^c^E: assessment of well-trained evaluator.

^d^S: participant self-report.

^e^EP: electrophysiological data.

#### Primary Outcome Measure

Fugl-Meyer assessment Upper extremity motor function was assessed with the FMA (range 0-66 points, total score) [30,31]. FMA consisted of test A (shoulder/elbow/forearm: 36 points, A score), test B (wrist: 10 points, B score), test C (hand/finger: 14 points, C score), and test D (coordination: 6 points, D score). FMA was assessed according to the scoring manual [32], and the validity and reliability were previously confirmed [31,33].

The estimated clinically important difference of the FMA-UE scores ranged from 4.25 to 7.25 points in individuals with stable, mild to moderate upper extremity hemiparesis [34]. However, MCID for patients with severe hemiparesis remains to be shown. As a greater than 10% change in FMA motor scores may represent a clinically meaningful improvement based on clinical experience [35], MCID for severe hemiparesis may be lower than that for mild hemiparesis. A minimal detectable change of 3.2 points was reported in 31 patients with stroke [36].

#### Secondary Outcome Measures

##### Action Research Arm Test

Action Research Arm Test (ARAT) [40] is a frequently used, validated, and reliable measure of upper extremity function with 4 subsections: grip, grasp, pinch, and gross movement [41,42]. The maximum summed score is 57.

##### Motor Activity Log-14

Upper extremity disability in activities of daily living (ADL) was assessed with Motor Activity Log (MAL), which uses a structured interview [43]. MAL includes 14 items, scored on an 11-point amount of use scale (range 0-5) to rate how much the arm is used (MAL-amount of use) and an 11-point quality of movement scale (range 0-5) to rate how well the participants are using their affected upper extremity [43]. High construct validity and reliability have been reported in patients with chronic stroke [43,44].

##### Motor Scores of the Stroke Impairment Assessment Set

The Stroke Impairment Assessment Set (SIAS) is a comprehensive instrument for assessing stroke impairment with well-established psychometric properties [45,46]. SIAS assesses various aspects of impairment in stroke patients, including motor function, tone, sensory function, range of motion, pain, trunk function, visuospatial function, speech, and sound side function. Motor scores of the SIAS are composed of 5 items that assess arm, finger, hip, knee, and ankle functions and are rated from 0 (severely impaired) to 5 (normal).

##### Goal Attainment Scale

The Goal Attainment Scale (GAS) is a self-rating scale to evaluate subjective improvement following rehabilitation [47-50]. Patients rate the attainment level of the rehabilitation outcome for the goal that they set themselves. If the attainment is as expected, it is rated as 0. Improvement beyond expectation is rated +1 or +2 and that below expectation is rated −1 or −2.

##### Barthel Index

The Barthel Index (BI) is one of the most frequently used measures to evaluate ADL in stroke research [51,52]. BI measures independence in ADL; the maximum score is 100. The 10 assessed items of ADL are feeding, bathing, grooming, dressing, bowel control, bladder control, toilet use, transfers, mobility, and ascending and descending stairs.

##### Modified Ashworth Scale

Spasticity at the wrist and finger flexors of the affected upper extremity was assessed with the Modified Ashworth Scale (MAS), a 6-point rating scale used to measure passive muscle resistance [53].

##### Stroke-Specific Quality of Life Scale

The Stroke-Specific Quality of Life Scale (SS-QOL) was developed to assess health-related quality of life in stroke patients [54,55]. SS-QOL contains 49 items and covers 12 different areas of quality of life affected by stroke. The 12 areas of the SS-QOL are energy, family roles, language, mobility, mood, personality, self-care, social roles, thinking, upper extremity function, vision, and work or productivity. Each area can be scored separately, but a total score is also available. The possible range of all scales is from 1 to 5, where a lower value indicates a lower health-related quality of life.

##### Surface Electromyography

The muscle activities of the paretic extensor digitorum communis and flexor digitorum superficialis muscles were recorded with Ag-AgCl surface electrodes with diameters of 9 mm (Nihon Kohden, Tokyo, Japan). The electrodes were applied with center-to-center spacing of 30 mm and were placed parallel to the muscle fibers and distal from the motor points of individual muscles. Before the electrodes were attached, the skin areas were rubbed with alcohol. Skin resistance was kept below 5 kΩ. An MEB-2300 EMG machine (Nihon Kohden) was used to record and analyze the EMG data. The bandpass filter was set at 20 Hz to 1 kHz. The patients were seated in a comfortable chair with their arms on an armrest and the angle of their elbows was kept at 70 to 90 degrees. They were instructed to rest for 5 seconds and then to extend their affected fingers for the next 5 seconds for 1 cycle. In total, 5 cycles of 5 seconds of rest and 5 seconds of extension were repeated.

##### Electroencephalogram During Brain-Machine Interface or Image Training

The EEGs during BMI or image training were recorded and stored in the EEG-BMI system. We compared the magnitude and duration of μERD between the BMI group and control group.

#### Statistical Analyses

The following 2 analysis populations are defined in this clinical trial. Statistical analyses were performed for each patient population.

The Full Analysis Set (FAS) essentially included all randomized patients, in accordance with the intention-to-treat principle, except for the following patients who violated major conditions in this study:

Patients who did not meet major inclusion criteria in this trialPatients who did not receive any study treatmentPatients who had no baseline measurements or no measurements after baselinePatients who withdrew informed consent after randomization and refused to generate any data in this trial

The Per Protocol Set (PPS) included patients who were compliant with the protocol and are defined in the patient-data handling document that will be finalized before the unblinding of this trial.

The primary analysis population in this trial is the FAS. The primary endpoint, a change from baseline in FMA at 28 days after study treatment, will also be analyzed for the PPS. The sensitivity of the primary analysis results will be examined via a comparison of results between the 2 analysis sets. All patients who received at least one study treatment are included in the safety analysis. The patient-data handling document, including the data handling rule for measurement at each time point, will be finalized before the unblinding. Methods to handle missing data will also be included in the statistical analysis plan (SAP) for this trial. Demographic factors and baseline characteristics are summarized by the treatment group.

#### Efficacy Analysis

##### Analysis of the Primary Endpoint

The primary endpoint of this trial is a change from baseline in the FMA at 28 days after study treatment. The superiority of the BMI group compared with the control group in terms of the primary endpoint will be demonstrated by means of an analysis of covariance model, which contains the baseline as a covariate and treatment group as a factor. Least squares means for the changes in treatment groups will be estimated and compared between the 2 groups. Missing data at 28 days after study treatment will be handled by multiple imputation, Rubin, which assumes missing at random as the missing data mechanism [56]. The details of the imputation model in the multiple imputation will be described in the SAP before the unblinding.

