## Methods

### Study Design

This is a single-blinded, multicenter RCT using a parallel arm design to evaluate the effectiveness and safety of 2-week BMI rehabilitation combined with intensive occupational therapy compared with motor imagery without any feedback and dose-matched occupational therapy. Overall, 4 hospitals in Japan participated in this trial. Patients were randomly assigned to either the BMI group or control group. The assessors were blinded, but patients were not. The primary outcome measure was change in upper extremity score of FMA between baseline and 4 weeks after the intervention.

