### Randomization

Participants were randomly allocated to the BMI or the control group using a computerized block randomization scheme, including prestratification according to each participating hospital.

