##### Analysis of Secondary Endpoints

For continuous endpoints, the same analysis model will be applied. For binary endpoints, 95% CIs for proportions by treatment groups will be estimated with the Clopper-Pearson method. The proportions of the 2 groups will be compared with Fisher exact test.

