##### Rationale

The mean changes from baseline in the FMA at 28 days after study treatment are assumed to be 6.9 and 3.0 in the BMI and control groups, respectively, based on previous clinical studies [57,58]. The SD for the change is also assumed to be 4.0. Under these assumptions, 17 patients per group results in 80% power for testing the between-group difference in means with a two-sided 5% alpha. Taking into account 15% exclusions from the analysis, the target sample size in this trial was set at 20 patients per group (total of 40 patients).

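### Randomisation is blocked within four hospitals but the stated ANCOVA omits hospital, so if hospitals differ materially the primary test is conservative and precision is forgone

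*Protocol article*

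**What the plan says.** Under Randomization, the article describes a "computerized block randomization scheme, including prestratification according to each participating hospital". Study Design gives the number of strata: "Overall, 4 hospitals in Japan participated in this trial".

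Under Analysis of the Primary Endpoint, the endpoint is fixed ("The primary endpoint of this trial is a change from baseline in the FMA at 28 days after study treatment"), and superiority is to be shown with an analysis of covariance "which contains the baseline as a covariate and treatment group as a factor". That section leaves the details of the imputation model to the SAP, but it states the terms of the ANCOVA outright.

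Under Analysis of Secondary Endpoints: "For continuous endpoints, the same analysis model will be applied". No section adds hospital to a model or gives a reason for leaving it out.

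**The concern.** Blocking within hospital makes the arms nearly equal in size at each site, so differences between hospitals largely cancel out of the treatment comparison. A model without hospital does not know this. It leaves the between-hospital variation in the residual and carries it into the standard error. The design removes a source of noise and the analysis puts it back.

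If hospitals do differ in FMA change, the confidence interval is wider than it need be and the true type I error falls below the nominal 5%. Some of the precision bought by stratifying is not used. The trial has 40 patients, about 80% planned power and one primary test. It is also meant to support regulatory approval, so a few points of power are worth having. Because the terms are stated, this is a choice to question and not a detail left to the SAP.

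**Working it through.** **Inputs from the article.** Four hospitals (Study Design). Mean changes "are assumed to be 6.9 and 3.0 in the BMI and control groups, respectively", a difference of 3.9; "The SD for the change is also assumed to be 4.0" (Rationale). 17 evaluable and 20 randomised per group, 15% exclusions (Rationale). Two-sided 5% (Significance Level and Multiplicity).

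**Assumptions, not in the article.** The between-hospital share of variance ρ, taken from 0 to 0.30; block size 4; the hospital sizes.

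**1. The plan's own figure.**
- n = 2 × (1.96 + 0.842)² × 4.0² / 3.9² = 2 × 7.85 × 16 / 15.21 = 16.5, so 17 per group.
- 17 / 0.85 = 20 per group.
- SE = 4.0 × √(2/17) = 1.372. Power = Φ(3.9/1.372 − 1.96) = Φ(0.88) = 0.811, or 0.787 with the noncentral t.

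The stated 17 and 20 reproduce.

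**2. Mechanism, with complete blocks.** Reading 4.0 as the total SD, the stated model reports about 4.0 × √(2/17). The true SE is about 4.0 × √(1 − ρ) × √(2/17). The reported SE is therefore too large by a factor 1/√(1 − ρ), and the actual type I error is about 2Φ(−1.96/√(1 − ρ)):

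| ρ | SE factor | type I error, formula | type I error, simulated |
|---|---|---|---|
| 0.10 | 1.05 | 3.9% | 3.7% |
| 0.20 | 1.12 | 2.8% | 3.1% |
| 0.30 | 1.20 | 1.9% | 1.8% |

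**3. Power with complete blocks.** Simulation, 34 evaluable patients at 10/8/8/8, 5,000 trials per cell (Monte Carlo error about √(0.8 × 0.2/5000) = 0.6 points). The share is held fixed in every simulated trial.

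| ρ | 4.0 = total SD: without / with hospital | 4.0 = within-hospital SD: without / with hospital |
|---|---|---|
| 0 | 78.1% / 77.8% | 78.0% / 77.5% |
| 0.02 | 77.8% / 78.0% | 76.6% / 76.7% |
| 0.10 | 77.6% / 80.4% | 73.3% / 77.0% |
| 0.20 | 79.9% / 85.7% | 70.5% / 78.1% |
| 0.30 | 80.6% / 89.9% | 64.2% / 77.1% |

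**4. Power with losses.** 40 randomised in blocks of 4, 6 lost at random, 4.0 as total SD. Losses and part-filled blocks disturb the balance within hospitals.

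| ρ | roughly even hospitals: without / with | 22/10/6/2: without / with |
|---|---|---|
| 0 | 78.1% / 76.1% | – |
| 0.05 | 77.8% / 78.0% | 78.4% / 77.2% |
| 0.10 | about 79% / 80–81% | 79.5% / 79.1% |
| 0.20 | about 80% / 84–85% | 81.7% / 83.7% |
| 0.30 | 81–82% / 88–89% | – |

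Type I error without hospital falls to about 3% to 4% at the larger shares.

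The gains also depend on how ρ is imposed. Step 4 fits four hospital effects drawn at random, so that the realised share varies from trial to trial. With the share held fixed, hospitals of 20/10/6/4 and the same losses give 77.6% / 79.6%, 77.7% / 83.8% and 79.9% / 89.0% at 10%, 20% and 30%: gains of 2, 6 and 9 points. The figures give an order of magnitude only.

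**The case against.** The strongest reply is that nothing in the article shows hospitals differ enough to matter. Eligibility is narrow, therapists were trained by the research team and sessions visited, and the FMA is scored to a manual. The outcome is change adjusted for baseline, which takes out stable differences in level between sites. The text does not say whether raters differed by site. With about 34 evaluable patients and hospital sizes unstated, a sparse model is defensible, and a positive result under it stands. This holds, and it limits the size of the point. It does not remove the mismatch between design and model.

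Four stronger readings are tempting, and the documents do not support them.
- *Power is lost whenever hospitals differ.* Below a share of about 5% (about 10% with very uneven hospitals), the 3 degrees of freedom and the residual imbalance offset any gain.
- *The trial is underpowered as a result.* If 4.0 is the total SD, power without hospital stays near 80% and the loss is a forgone gain. It falls clearly short only if 4.0 is a within-hospital SD, and the Rationale does not say which is meant.
- *The result is biased or false positives are more likely.* The error runs the other way.
- *The imputation model is deficient.* Its details are expressly left to the SAP, which is not shown.

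**Conclusion.** The mismatch is in the text and is certain: randomisation is stratified by hospital and the stated ANCOVA omits it, for the primary and the continuous secondary endpoints. The direction is also clear: standard errors too large and a conservative test if hospitals differ materially.

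The magnitude is conditional on the assumed share. On the step 4 assumptions with roughly even hospitals, the power forgone is about 1 to 2 points at 10%, 4 to 5 at 20% and 6 to 7 at 30%. It is less with very uneven hospitals when the hospital effects are drawn at random, and somewhat more with the share held fixed. If 4.0 is a within-hospital SD, the complete-block figures are about 4, 8 and 13 points, and power without hospital is 73%, 71% and 64%. This is a moderate point of efficiency and consistency and does not threaten validity.

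**What to change.** Before unblinding, add hospital as a fixed factor to the primary ANCOVA and to the continuous secondary analyses. State in advance how a hospital with very few patients is pooled, and keep the SAP's imputation model consistent with the analysis model. The article says that the SAP is finalised before unblinding and that changes to it are reported, so the change can be pre-specified; made later, it would look data-driven.

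The cost is a line in the SAP and 3 degrees of freedom. If hospitals do not differ at all, power falls by about 0.5 points with complete blocks and by about 1 to 2.5 points with part-filled blocks and losses.
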